## **Research program TREND study: Treatment of NAFLD using two diets**

### **Summary**

- Fatty liver (NAFLD) is the most common liver disease in the world
- Only a few patients manage to lose weight to the extent needed (>10%) to reduce the amount of fat in the liver
- It is unknown which diet method is most effective in reducing the amount of fat in the liver of patients with NAFLD
- In animal models and some studies in humans, a high-fat diet has been shown to lead to increased fat in the liver
- In this intervention study, we compare how two isocaloric diets with different fat content - periodic fasting (5: 2) and low-carbohydrate high-fat diet (LCHF) - affect the liver in patients with NAFLD

### **Background**

Fat retention in the liver (non-fatty alcoholic liver disease, NAFLD) is the world's most common liver disease that affects approximately 15-30% of the population. Moreover, it is closely linked to obesity and insulin resistance (1,2). Brown and Goldstein have shown that high insulin production (such as insulin resistance) stimulates the production of triglycerides in the liver and the development of liver steatosis, which may be an explanation for why NAFLD is associated with diabetes mellitus type 2 and cardiovascular disease (3). Some 3-5% of patients with NAFLD develop liver cirrhosis (4). At present, there is no medical treatment for NAFLD, but the most effective method of treatment is weight loss. A weight loss of 10% or more leads to better insulin sensitivity and a reduction of fat content in the liver by nearly 100%, which reduces the risk of developing liver cirrhosis. Unfortunately, such weight loss can only be achieved in 10-20% of patients (5). There is currently no structured care for this large patient group, but usually patients are informed that they should lose weight after the diagnosis of NAFLD has been determined. How this should be done is often left to the patients themselves, which can lead to a lack of motivation and poor results. Many patients want to use one of the popular weight-loss diets, such as calorie restriction (CR) with periodic fasting (so-called 5:2 diet) or low carbohydrate high-fat diet (so-called low-carb high-fat, LCHF).

Several studies have shown that CR reduces the risk of cardiovascular disease and diabetes.

Animal studies have shown that CR reduces IGF1 levels, the risk of cancer and prolongs life

(6-8). Under a long time, CR lowers blood pressure, blood sugar and blood pressure. A study has shown that a reduced incidence of atherosclerosis (atherosclerosis) is linked to CR and not to weight loss per se (9). Periodic CR, according to the so-called 5:2 diet, means that during two of the days of the week, a maximum of 25% of the daily caloric intake is recommended (i.e. about 500-600 kcal); during the other days of the week, food intake is optional, but with an emphasis on the so-called Mediterranean diet. Only a few studies have evaluated the effect of periodic CR on healthy people with overweight and patients with type-2 diabetes.

The low-carb-high-fat (LCHF) diet involves a reduction in intake of carbohydrates and a compensatory increase in fat intake. LCHF is a diet that has been widely applied in recent years, and which is popular with obese people for losing weight (13). Thus far, the scientific basis for the LCHF diet is sparse, but a similar diet (the Atkins diet) has been shown to reduce weight slightly more than comparable diets (14). In a Danish study, high-fat diets gave a more favorable lipid profile in serum than low-fat diets rich in carbohydrates (15). In animal models, however, a high-fat diet leads to increased fat retention in the liver (16, 17). The composition of fatty acids in the diet may have an impact on fat retention in the liver. Ingestion of muffins enriched with saturated fatty acids resulted in a significant increase in fat retention in the liver and visceral fat compared to the intake of muffins enriched with polyunsaturated fatty acids (18). However, in this study, patients ate more than normal, and it is unknown whether saturated fats have the same effect at concomitant calorie restriction. In one study, visceral fat and metabolic syndrome were not affected by dietary fat (19). In contrast, in other studies, dietary treatment with a high proportion of fat in the diet (55-60% E% fat) compared to low fat in the diet (16-20 E%) has led to more pronounced fat retention in the liver (20, 21).

Thus, there are no studies that have evaluated the effects of periodic fasting or LCHF diet on fat retention in the liver, liver enzymes, liver elasticity or insulin sensitivity in patients with NAFLD.

### **Purpose**

To investigate in a randomized, controlled study whether two common diets, the 5:2 and LCHF diet, can reduce the amount of fat in the liver, liver enzymes, liver stiffness and insulin resistance in patients with NAFLD compared to placebo (in the form of standard advice on nutritional intake). A further aim was to determine whether any of these diets have a greater effect than the other.

### **Primary outcome measure**

- Reduction of fat in the liver, measured by MRI after 3 months of treatment with either the LCHF diet, the 5:2 diet, or placebo.

### **Secondary outcome measures**

- Reduction of liver stiffness and liver fat as measured by elastography (FibroScan).
- Reduction of liver enzymes (ASAT, ALAT).
- Weight reduction.
- Altered body composition as measured by MRI, BIA and MAMC/TSF.
- Improvement in insulin sensitivity as measured by IR-HOMA, IGFBP-1 and Adiponectin.

### **Inclusion criteria**

- Diagnosed NAFLD through
  - findings of liver steatosis in radiology

- or a transaminase increase without any other known or suspected liver disease, in combination with obesity ( $\text{BMI} \geq 30$ ) and at least one parameter in the metabolic syndrome, and with controlled attenuation parameter (CAP)  $> 280$  in FibroScan
- Can understand Swedish to the extent necessary to comprehend the purpose and method of the study
- Signing the informed consent form

### **Exclusion criteria**

- Diabetes mellitus type-1 or type-2 treated with insulin, GLP-1 agonists or sulfonylurea preparations (NOTE! metformin treatment is allowed)
- Other liver diseases known or detected during screening
- Other known or suspected causes of fat deposits in the liver
- Consumption of alcohol over 140 grams per week (10 standard units) for women and over 210 grams per week (15 standard units) for men
- Established liver cirrhosis in radiology, FibroScan or liver biopsy
- Chronic kidney disease stages 4 and 5 ( $\text{Pt-eGFR} < 31 \text{ ml/min}$ )
- Pregnant and nursing women
- Implanted metal (e.g., pacemaker, aneurysm clips)
- Claustrophobia
- Participation in other clinical trials for NAFLD
- Tested any of the intervention methods within six months before screening

### **Method**

Patients are recruited via three routes: (1) patients with known NAFLD who are followed at the liver clinic at the Gastro center; (2) patients referred to the Gastro center from primary care for investigation of suspected NAFLD; and (3) by an advertisement in the local press

(see Appendix 1). Patients are called to a doctor's appointment at the liver clinic where they are informed about the study orally and in writing.

Patients who meet the inclusion criteria and sign the informed consent form are screened for any exclusion criteria. After screening and inclusion, baseline tests are performed (specified below). A total of 75 patients, balanced for sex, will be randomized to either treatment with the LCHF diet, 5:2 diet, or placebo (see below). The diet intervention takes place in collaboration with [name]'s research group at Karolinska. Solna by dietitians and doctors. Methodology and infrastructure have been developed through other diet intervention studies, with logistics that have been tested on >100 patients with and without type2 diabetes. At both the start and conclusion of the study, the liver's fat content is checked with an MRI and liver stiffness with elastography. Differences in fat content and liver stiffness will be statistically analyzed using the rank-sum-test primarily according to the intention-to-treat principle as well as in sensitivity analysis by the per-protocol principle.

Because there are no data on the effect of diets on the reduction of liver fat, it is difficult to perform a power analysis. If data are extrapolated from other weight loss interventions where liver fat data are available and assume that dietary intervention groups will lose approximately 5% of their weight over three months, this represents approximately 30% reduction in liver fat. Assuming that the placebo group reduces the amount of fat in the liver by 10%, and with a standard deviation of 20%, at least 16 people in each arm will be needed to see differences between the groups with 80% power and an alpha value of 0.05. Because some loss of participants can be expected to occur, we want to include 25 people in each arm.

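### The primary rank-sum test is fixed on an undefined difference in liver fat and without baseline adjustment, while the sample size assumes percent reductions

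*Protocol*

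**What the plan says.** All of the statistical text stands in the Method section of the protocol.

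- **Primary analysis:** "Differences in fat content and liver stiffness will be statistically analyzed using the rank-sum-test primarily according to the intention-to-treat principle". A per-protocol analysis serves as sensitivity analysis. No covariate is named.
- **Measurement:** the sentence before this says that, at both the start and the end of the study, the liver's "fat content is checked with an MRI and liver stiffness with elastography". The Baseline samples section includes the MRI scan, and the Randomization and dietary treatment section places randomization after the baseline samples.
- **Outcome:** the Primary outcome measure section gives "Reduction of fat in the liver, measured by MRI after 3 months of treatment", without a scale.
- **Sample size:** for the diet arms, a 5% weight loss is taken to mean that "this represents approximately 30% reduction in liver fat" follows. For the control arm: "Assuming that the placebo group reduces the amount of fat in the liver by 10%, and with a standard deviation of 20" per cent. From this come 16 per arm for 80% power at alpha 0.05, raised to 25 per arm for expected losses.
- **Sex:** "A total of 75 patients, balanced for sex, will be randomized". The randomization section gives a 1:1:1 ratio and does not mention sex.

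**The concern.** A difference in fat content can be a change in percentage points of liver fat or a change as a percentage of the patient's own baseline. These are different endpoints. A fall from 20% to 16% liver fat and a fall from 5% to 4% are the same relative change, but the absolute changes are 4 points and 1 point. Absolute change therefore carries the spread of baseline fat as extra noise, and a power calculation in relative terms does not carry over to it. With the scale open, the power of the primary test is unknown and the choice could be made after the data are seen.

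The second issue is that baseline liver fat will be on file before allocation, yet the named test cannot use it as a covariate. If baseline predicts how far a patient responds, the trial gives away precision that it has already paid for.

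**Working it through.** **1. Reproduce the protocol's figure.** Inputs from the Method section: difference 30 − 10 = 20 points, SD 20, power 80%, alpha 0.05 (taken as two-sided).

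n per arm = 2 × (1.960 + 0.842)² × (20/20)² = 2 × 7.85 = 15.7, rounded up to **16**. The figure reproduces, by a formula for means on the percent-change scale.

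**2. The named test on that scale.** The t-test version needs 16.7. With the rank-sum test's asymptotic efficiency of 0.955 for normal data, the need is 16.7/0.955 = 17.5, so 18 per arm. Approximate power is 76% at 16 per arm and 92% at 25. Keeping 18 of 25 allows a loss of 7/25 = 28%.

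**3. Effect of the scale and of adjustment, by simulation** (2,000 runs per setting; Monte Carlo standard error at most about 1.1 points). From the protocol: percent reductions of mean 10 and 30, SD 20. Assumed, because the protocol gives neither:

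- baseline liver fat is lognormal with median 12% and coefficient of variation (CV) 0.4 or 0.6;
- the correlation ρ between (log) baseline and percent reduction is 0 to 0.5, a positive value meaning that fattier livers lose proportionally more.

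The adjusted analysis is an ANCOVA of percent change on arm and log baseline fat. Power in %:

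| n per arm | CV | ρ | Rank-sum, percent change | Rank-sum, absolute change | ANCOVA, percent change |
|---|---|---|---|---|---|
| 16 | 0.4 | 0 | 76.4 | 69.1 | 77.9 |
| 16 | 0.4 | 0.3 | 75.5 | 61.4 | 81.1 |
| 16 | 0.4 | 0.5 | 74.0 | 56.9 | 87.2 |
| 16 | 0.6 | 0 | 75.2 | 62.1 | 76.5 |
| 16 | 0.6 | 0.3 | 75.1 | 56.8 | 81.2 |
| 16 | 0.6 | 0.5 | 74.3 | 51.7 | 86.6 |
| 25 | 0.4 | 0 | 92.2 | 87.0 | 93.4 |
| 25 | 0.4 | 0.3 | 92.3 | 81.5 | 95.1 |
| 25 | 0.4 | 0.5 | 91.5 | 77.6 | 97.6 |
| 25 | 0.6 | 0 | 92.1 | 83.7 | 93.4 |
| 25 | 0.6 | 0.3 | 92.0 | 75.8 | 95.0 |
| 25 | 0.6 | 0.5 | 93.5 | 72.5 | 98.0 |

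With a CV of 0.8, the absolute-change column falls as low as 46% at 16 per arm and 67% at 25.

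**4. Gain from adjustment, on percent change.** At ρ = 0: 77.9 − 76.4 = 1.5 and 76.5 − 75.2 = 1.3 points at 16 per arm, with about the same at 25. At ρ = 0.5: 87.2 − 74.0 = 13.2 and 86.6 − 74.3 = 12.3 points at 16 per arm; 97.6 − 91.5 = 6.1 and 98.0 − 93.5 = 4.5 at 25. The closed form points the same way: multiplying the variance by 1 − ρ² = 0.75 lowers the need from 15.7 to 15.7 × 0.75 = 11.8, so 12 per arm.

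**5. Does the remedy survive near-complete responders?** The Background section says that weight loss of 10% or more removes nearly all liver fat and is reached by 10-20% of patients. Assume that 10% of diet-arm patients have reductions of 90-99%. At 16 per arm, the rank-sum test on percent change then has about 83% power and an ANCOVA of log 3-month fat about 75%, because logs of values near zero are extreme. Across settings with and without such patients (CV 0.4-0.6), ANCOVA of percent change was never below the rank-sum test on percent change: 77-94% against 74-85% at 16 per arm, and 93-99% against 91-97% at 25. The rank-sum test on absolute change had 50-78% and 71-93%.

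**The case against.** The strongest case on the other side is that the planned test is sound. Liver fat is measured at both ends and the outcome is a reduction, so the differences are most naturally within-patient changes, and baseline already enters by subtraction. The only numerical meaning that the protocol gives to a reduction is a percentage. On that scale, 25 per arm gives about 92% power before losses. A rank test is a reasonable choice for a small and possibly skewed sample. Covariates and confidence intervals are commonly left to a statistical analysis plan, which is not shown here.

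Most of this stands, and it rules out several stronger readings that a reader might infer:

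- *That the analysis ignores baseline fat.* The text does not support this. Baseline is probably subtracted; it is not adjusted for.
- *That the test is on the wrong scale.* The scale is unstated, so there is a gap between two statements but no proven contradiction.
- *That only 3-month values are compared.* Simulated power would then be about 15-51% at 16 per arm (CV 0.4-0.8), but an outcome worded as a reduction does not point to that reading.
- *That the rank-sum test as such wastes power or is biased by chance imbalance.* On percent change with ρ = 0, it is within 2 points of the adjusted analysis, and randomization protects its type I error.
- *That sex must be a covariate.* The phrase on balance for sex may describe recruitment, since the randomization section names no stratification.

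Two things remain. The protocol commits to a primary test without fixing what is tested, and that test cannot adjust for a baseline measurement already planned for every patient. These are features of a stated method, not detail deferred to another document.

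**Conclusion.** The point holds as a cheap improvement to a valid test. The firm part is textual: the primary analysis has no defined scale, and the power statement applies only to the relative one.

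The size is conditional. If the test is run on absolute change, power at 16 per arm is about 50-70%, not the stated 80%, for an assumed baseline CV of 0.4-0.6, ρ of 0-0.5 and no near-complete responders. The loss would be smaller if patients with more baseline fat responded proportionally less, because absolute change would then vary less. If the test is run on percent change, power is about 75% at 16 per arm and 92% at 25, so the planned 25 per arm protects the 80% target unless losses approach 30%.

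The gain from baseline adjustment lies between almost nothing (ρ = 0) and about 13 points at 16 per arm or 6 at 25 (ρ = 0.5). The protocol gives no value for ρ or for the spread of baseline fat.

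**What to change.** 1. Define the primary endpoint as percent change in MRI liver fat from baseline to 3 months, which matches the sample size calculation.
2. Make the primary analysis an ANCOVA of that percent change on arm and baseline liver fat, adding sex if sex is used to balance the allocation. Baseline may enter on the log scale, as in the simulations above.
3. Report the difference in percent reduction with a 95% confidence interval for each pairwise comparison, so that the result can be set against the planned 20 points.
4. Keep the rank-sum test, or a rank-based ANCOVA, on percent change as sensitivity analysis.
5. Do not make a model for log 3-month fat primary, because near-complete fat loss gives extreme log values.

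The cost is a few lines of protocol text and a standard model on data already planned. The one drawback is a distributional assumption, which the rank-based analysis checks. The change should be made before outcome data are seen by arm.

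### The 80% power at 16 per arm holds for one unadjusted comparison of means, not for the rank-sum test or the several comparisons that the protocol sets out

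*Protocol*

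**What the plan says.** The protocol's Primary outcome measure section names one outcome, reduction of liver fat by MRI at 3 months, across three arms: LCHF, 5:2 and placebo (standard advice). The Purpose section asks whether the two diets do better than placebo, and then adds: "A further aim was to determine whether any of these diets have a greater effect than the other".

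The Method section fixes the test: "Differences in fat content and liver stiffness will be statistically analyzed using the rank-sum-test". It does not list the pairs to be compared.

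The power paragraph in the same section assumes a 30% reduction in liver fat for the diet groups, 10% for placebo and a standard deviation of 20%. It concludes that "at least 16 people in each arm will be needed to see differences between the groups with 80% power" and "an alpha value of 0.05". The plan is to include 25 per arm (75 in all) because some participants will be lost. No loss rate is given.

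**The concern.** Two things in the Method section do not fit together. The size of 16 comes from a formula for comparing two means, while the stated analysis is a rank test, which needs slightly more patients under the same assumptions. The paragraph also speaks of differences between the groups, in the plural, but the calculation covers one diet against placebo with the whole alpha of 0.05.

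At stake is what the 80% can be taken to mean. A reader would suppose that the trial still has its stated power for its stated test if each arm falls to 16 evaluable patients. A reader would also suppose that the 5% error rate applies to the primary outcome as a whole. The first does not hold. The second depends on rules that the protocol does not give.

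**Working it through.** **Inputs (protocol, Method).** Reduction 30% on either diet and 10% on placebo, so the diet-placebo difference is 20 points; SD 20; standardised difference 20/20 = 1.0. Alpha 0.05, power 80%. Sidedness is not stated. Two-sided is assumed because it reproduces the protocol's figure (one-sided gives 13). Data are taken as normal, in line with the mean and SD inputs.

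**1. The protocol's figure.**
n = 2 × (z₀.₉₇₅ + z₀.₈₀)² × (SD/difference)² = 2 × (1.960 + 0.842)² × 1 ≈ 15.7, so 16 per arm.
Power at 16 = Φ(√(16/2) × 1.0 − 1.960) = Φ(0.868) = 80.7%.
So 16 is correct for one two-sided, unadjusted comparison of means by the normal formula.

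**2. The test that the protocol names.**
- The t-test needs 16.7, so 17 per arm; its power at 16 is 78.1%.
- The rank-sum test under normality needs about the t-test size times π/3: 16.71 × 1.047 = 17.5, so 18 per arm.
- Simulation of the rank-sum test gives 75% power at 16 and 80% at 18 for one diet-placebo comparison. The chance that both diets beat placebo at 16 per arm is 62%.

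**3. Error rate if each pair is tested at 0.05 with no global test first.**
- Three pairs: the probability that the studentized range of three arms exceeds 1.960 × √2 = 2.772 is 12.2%. Simulated rank-sum tests give 11.5% to 12.3% at 16 to 25 per arm.
- The two diet-placebo pairs only: 8.5% to 9.1% by simulation.

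**4. Diet versus diet.** Both diets are assigned the same 30% reduction, so the assumed difference is zero and the rejection rate is about 5%, the error rate alone. For scale, true differences of 10 and 5 points are assumed here (neither is in the protocol), with the normal formula:

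| True diet-diet difference | Power at 16/arm | Power at 25/arm | Per arm for 80% |
|---|---|---|---|
| 10 points | 29% | 42% | 63 |
| 5 points | 11% | 14% | 252 |

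**5. Kruskal-Wallis at 0.05 first, then pairwise rank-sum tests at 0.05 only if it rejects.** With three arms, any two pairwise nulls together imply that all three arms are equal. The global test therefore covers every joint null, and this is a valid closed procedure. Simulated family-wise error is 4.7% to 5.0%.

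| Evaluable per arm | Power per diet-placebo comparison, global test first | Same, without it |
|---|---|---|
| 16 | 70% | 75% |
| 19 | 79% | 83% |
| 20 | 81% to 82% | 85% |
| 25 | 90% | 92% |

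**6. Loss that 25 per arm can absorb.** Down to 20: 1 − 20/25 = 20%. Down to 18 (one comparison, no global test): 1 − 18/25 = 28%. Down to the protocol's 16: 1 − 16/25 = 36%.

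**The case against.** - **The protocol does not commit to three equal tests.** It lists no pairs and states 0.05 only within the sample-size assumptions. It places the diet-diet question second, as a further aim. Order, a global test or alpha sharing are normal SAP content, and the SAP is not shown. This stands. A reader might infer that the trial has a 12% chance of a false claim, but the documents support that figure only on condition that three pairs are tested at 0.05 without further control.
- **The 12% also counts results that nobody would claim as benefit.** It includes diet-diet rejections and cases where a diet looks worse than placebo. If no arm differs, the chance of falsely declaring at least one diet better than placebo, from two unadjusted two-sided tests, is only 4.2% to 4.6% at 16 to 25 per arm. This stands as a limit on how the figure may be read. Whether separate diets sharing one control need joint error control is itself debated.
- **Sixteen is not an arithmetic slip.** It reproduces exactly, and two more patients per arm is small beside the uncertainty in an effect that the protocol itself says is hard to power for. This stands as to size, but the stated 80% still does not belong to the stated test.
- **The trial enrols 25 per arm, not 16.** A reader might infer that it is underpowered. With full retention, power per diet-placebo comparison is 92% unadjusted, 90% with a global test first and about 82% under a three-way Bonferroni split. The documents do not support a charge of underpowering.
- **The protocol claims no 36% loss allowance.** True: that is only the arithmetic of going from 25 to 16. No loss rate is given.

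**Conclusion.** The power statement is wrong as written. At 16 per arm the named test gives about 75% for one diet-placebo comparison and about 62% for both, and 18 per arm are needed for 80% on one. This follows from the Method section alone and needs no view on multiplicity. It rests on normal data, a two-sided 0.05 and a difference equal to the SD.

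The multiplicity part is real but conditional: about 12% for three pairs or 9% for two, if they are tested at 0.05 each with nothing in front and the SAP sets no rule. The diet-diet aim has no power basis under the protocol's own assumptions.

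The planned 25 per arm remains adequate for diet versus placebo with good retention. What shrinks is the margin for loss. This is a should-fix point, not a fatal one.

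**What to change.** Keep 25 per arm and amend the Method section (the first item may go in the SAP instead):

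1. Unless the SAP already controls the error across comparisons, make the primary test of liver fat a three-arm Kruskal-Wallis test at two-sided 0.05. Pairwise rank-sum tests at 0.05 are read only if it rejects.
2. Restate the size for that procedure: about 20 evaluable per arm for 80% power per diet-placebo comparison, so that 25 per arm tolerates about 20% loss. If the SAP instead makes one diet-placebo comparison primary, the figure is 18.
3. Say that the diet-diet comparison is exploratory as regards power.

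Settle this before results are seen, because an order or a global test chosen afterwards does not protect the primary claim. The cost is a few sentences, about 2 points of power per diet-placebo comparison at 25 per arm (90% against 92%), and a less favourable stated number.

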### **Risks**

There is a potential risk that the LCHF diet may lead to an increase in fat retention in the liver. However, given the concomitant calorie restriction, the risk is considered minimal. At the 6-week control, fat retention will be evaluated through blood tests (control of triglycerides

and liver enzymes). If ALAT, ASAT, ALP, or bilirubin rises >3 times baseline levels, diet treatment will be discontinued.

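### The increase from 16 to 25 per arm states no loss rate and keeps the full 20-point effect, so it is not matched to a rank-sum test under intention to treat

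*Protocol*

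**What the plan says.** All the sample-size reasoning stands in the protocol, section Method. The diets are expected to produce about 5% weight loss, and "this represents approximately 30% reduction in liver fat". The comparator and the spread follow: "Assuming that the placebo group reduces the amount of fat in the liver by 10%, and with a standard deviation of 20" percent. From these the protocol obtains at least 16 per arm "with 80% power and an alpha value of 0.05". The last step is "Because some loss of participants can be expected to occur, we want to include 25 people in each arm". No loss or non-adherence rate is given.

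The same section has liver fat measured by MRI at the start and the end, and compares the differences with a rank-sum test, "primarily according to the intention-to-treat principle". Per protocol is the sensitivity analysis. The section does not say how a patient without a final MRI is handled.

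Two other places bear on this. The section on investigations at 3 months schedules the MRI. The section Risks says that after a more than threefold rise in liver tests "diet treatment will be discontinued". It does not say that follow-up ends.

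**The concern.** Raising 16 to 25 restores the head count after loss. That is enough if lost patients simply drop out of the comparison and those who remain show the full effect. Intention to treat also keeps in their arm the patients who stopped the diet but still had the MRI. Depending on how missing MRIs are handled, it may also count patients who were lost. If such patients gain no benefit from the diet, the difference between arms shrinks, and a larger head count alone does not make up for it.

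In an open-label diet trial, loss and poor adherence are likely to go with little weight loss. If the real power is well below 80%, a null result could reflect dilution and would be hard to interpret. If instead only completers are compared, the estimate may favour the more demanding diets.

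A separate, smaller problem is that 16 is the normal-approximation answer for comparing two means, while the planned test is a rank-sum test, which needs slightly more patients.

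**Working it through.** **Inputs from the protocol (Method).** Mean reduction 30% on diet and 10% on placebo, so a difference of 20 points; SD 20 points; alpha 0.05; power 80%; 16 needed and 25 planned per arm. The protocol does not state sidedness. Two-sided reproduces its figure, while one-sided would give 13.

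**Step 1: reproduce 16.** n = 2(1.960 + 0.842)² × 20²/20² = 15.7, rounded up to 16. Power at 16: 20/(20√(2/16)) − 1.960 = 2.828 − 1.960 = 0.868, which is 80.7%. The stated figure reproduces.

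**Step 2: the largest loss that 25 can absorb by number.** (25 − 16)/25 = 36%, and 16/0.64 = 25. This rate is inferred; the protocol does not predict it.

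**Step 3: the planned test, completers only.** Simulated rank-sum power with normal data and the protocol's means and SD is 75% at 16 per arm, 80% at 18 and 92% at 25. (The t-test gives 78% at 16 and 81% at 17.) So about 18 completers per arm are needed, and the tolerable loss is (25 − 18)/25 = 28%.

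**Step 4: all 25 analysed, lost patients without diet benefit.** With a share L of such patients the difference becomes 20(1 − L). At L = 0.36 it is 12.8 points. Diluting the difference alone gives 12.8/(20√(2/25)) − 1.960 = 2.263 − 1.960 = 0.303, or 62%. If lost diet patients respond like placebo, the diet-arm variance also rises, to 400 + 0.36 × 0.64 × 400 = 492. Then 12.8/√((492 + 400)/25) − 1.960 = 0.183, or 57%.

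Rank-sum power by simulation, 25 randomised per arm, two-sided 0.05:

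| Lost or off diet | Lost diet patients respond like placebo | Lost patients in both arms set to no change |
|---|---|---|
| 0% | 92% | 92% |
| 12% (3 of 25) | 83% | 84% |
| 16% (4 of 25) | 79% | 81% |
| 20% (5 of 25) | 74% | 76% |
| 36% (9 of 25) | 53% | 53% |

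These rows fix the number lost. If each patient is instead lost at random with probability 14%, both columns give 80%.

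**Step 5: sensitivity to the assumption at 36%.** If lost patients in both arms have mean change 0 with SD 20, rank-sum power is 47%. The t-test gives 49-66% over the same three scenarios. The range is therefore 47-66%. Harsher rules, such as loss in the diet arm only or a worst rank for every lost patient, give less.

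**The case against.** A reader might infer that over-enrolling for loss contradicts an intention-to-treat analysis, or that power near 80% survives only if lost patients are left out. The documents support neither. Intention to treat fixes that patients are analysed as randomised; it does not fix how a missing MRI is treated. Analysing observed outcomes as randomised, or imputing under missing at random, is compatible with over-enrolment and keeps power near the completer figure. Even with dilution, power is about 80% at 14-16% loss.

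Nor does the plan expect 36% loss. It says only that some loss may occur, and 25 may be a rounded margin over a lower rate that is not written down.

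The assumed 30% is also tied to an expected weight loss in the intervention groups. It may already be a group average that includes poor adherers, in which case diluting it again counts non-adherence twice.

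Finally, rules for missing data usually belong in a statistical analysis plan, which is not shown here, so their absence from the protocol is not a defect.

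All of this stands, and it limits the point. It does not supply a loss rate, say whether the 30% applies to adherers or to everyone randomised, or make 16 completers enough for 80% with a rank-sum test. Patients who stop the diet but have the MRI stay in their arm whatever the missing-data method. If the 30% describes adherers only, an analysis plan cannot remove that dilution.

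**Conclusion.** The sample-size statement is not matched to the planned test and analysis set. With 25 randomised per arm, about 80% rank-sum power holds up to roughly 28% loss if only completers are compared. It holds up to roughly 14-16% loss or non-adherence if such patients are analysed without diet benefit. At the inferred maximum of 36%, the stated 80% is missed either way: about 75% for completers and about 53% (47-66% across assumptions and tests) for all 25.

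The figures rest on the protocol's means and SD, normal data and a two-sided test of one diet against placebo. The diluted figures also assume that the 30% is not already a group average. The 53% is a scenario at the edge of what 25 can absorb, not a forecast for this trial.

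**What to change.** 1. State the expected loss and non-adherence rate, and say whether the 30% reduction refers to adherers or to everyone randomised. Restate power for the rank-sum test on the intention-to-treat set. If the 30% refers to adherers: 92% at 0%, about 80% at 14-16%, about 74-76% at 20% and about 53% at 36%.
2. State that the 3-month MRI is sought from every randomised patient, including those no longer on the diet for any reason.
3. Adjust the primary comparison for baseline liver fat, which is already measured. The gain depends on the correlation between baseline and change, which the protocol does not give, so no figure is claimed. Add a sensitivity analysis for missing MRIs that uses the 6-week weight and liver tests already collected. The imputation details can stand in the analysis plan.

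The cost is protocol wording and a little more analysis. No extra patients or visits are needed. The downside is a less favourable stated power.
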